## Abstract

**Background**: Chronic low back pain (CLBP) is a common musculoskeletal disorder that significantly impairs quality of life and is frequently associated with vitamin D deficiency. Therapeutic exercise is a cornerstone of management, yet the optimal adjunct intervention to restore serum vitamin D levels remains uncertain. No prior randomized trial has compared oral vitamin D supplementation with lifestyle education on sun exposure, nutrition, and physical activity, both combined with therapeutic exercise. We hypothesize that therapeutic exercise plus an education booklet (TEB) may be superior to therapeutic exercise plus oral vitamin D supplementation (TED) in reducing pain and disability while improving serum vitamin D levels.

**Methods**: This assessor-blinded, two-arm, multicenter randomized controlled trial (RCT) will be conducted in hospitals and rehabilitation centers in Dhaka city, Bangladesh. Adult participants (18–65 years) with CLBP and confirmed vitamin D deficiency will be recruited and randomized to either TEB or TED groups. Both groups will receive standardized therapeutic exercise protocols. The intervention duration will be 6 months, with assessments at baseline, 2 months, and 6 months. Primary outcomes include pain intensity measured by the Brief Pain Inventory (BPI) and serum 25(OH)D3 levels. Secondary outcomes include disability assessed by the Roland-Morris Disability Questionnaire (RMDQ). Statistical analysis will follow the intention-to-treat principle, using repeated measures ANOVA to compare group differences over time.

**Discussion**: This trial will provide evidence on whether a multidimensional lifestyle-based education approach combined with therapeutic exercise offers greater benefit than vitamin D supplementation with exercise in CLBP patients with vitamin D deficiency. The findings will inform clinical guidelines and support comprehensive management strategies for CLBP, particularly in resource-limited settings.

Registration: Clinical Trials Registry India (
CTRI/2022/11/047074).

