Chronic low back pain (CLBP) has been associated with vitamin D deficiency, which affects calcium metabolism, bone health, and muscle function. Deficiency may lead to osteomalacia, muscle weakness, and impaired neuromuscular control, increasing spinal instability and pain. Additionally, low vitamin D levels can elevate pro-inflammatory cytokines, intensifying pain sensitivity and contributing to chronic musculoskeletal disorders.
^
8
^ Clinical studies have reported a higher prevalence of vitamin D deficiency among patients with CLBP compared to healthy controls, suggesting a potential association between deficiency and pain severity.
^
17,
18
^ Vitamin D supplementation has been explored as a supportive measure in CLBP due to its role in bone health, muscle strength, and inflammation regulation.
^
19
^ Correcting deficiency may improve musculoskeletal function and reduce pain sensitivity, with clinical trials reporting symptomatic improvement in deficient patients.
^
20,
21
^ However, meta-analyses indicate limited overall efficacy, suggesting benefits may be restricted to those with confirmed deficiency, while excessive intake carries risks such as hypercalcemia and kidney stones.
^
22
^

This study hypothesizes that multidimensional comprehensive management through therapeutic exercise combined with an education booklet on sun exposure, nutrition, and lifestyle (TEB) will be superior to therapeutic exercise with oral vitamin D supplementation (TED) in patients with chronic low back pain and vitamin D deficiency. Specifically, it is expected that participants in the TEB group will demonstrate greater improvements in pain symptoms, serum vitamin D levels, and disability status compared to those in the TED group, with these effects observed at both 2 and 6 months following baseline recruitment. Following the study hypothesis, this trial holds clear clinical significance: for clinicians, it offers evidence to guide treatment choices between exercise combined with education or vitamin D3; for patients, it evaluates accessible, low-cost strategies that may improve pain and function; and for researchers, it provides rigorous comparative data to inform future studies on scalable interventions for CLBP.

The specific objectives are:

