**Outcome measurement**

**
*Primary outcome*
**

*Pain*

The BPI (Brief Pain Inventory), comprising fifteen items, evaluates the degree of pain and how it affects everyday living. It measures pain interference in relationships, emotions, quality of life, and physical activities, including sleep, general activity, and walking; it also contains pain diagrams and questions regarding drugs and analgesics. Higher ratings indicate more acute pain and more interference.
^
30
^ With an interclass correlation coefficient (ICC) of 0.84–0.90 and kappa values over 0.70, the BPI exhibits great internal consistency (Cronbach's alpha = 0.91) and dependable test–retest results.
^
10
^

*Vitamin-D3 level*

Serum 25(OH) D will be used to measure the level of Vitamin D3. Tests will be advised by an expert physician, and researchers will collect information from laboratory test reports. Patients will be categorized based on vitamin D levels, such as deficient (less than 20 ng/mL); insufficient (21 to 29 ng/mL); and sufficient (more than 30 to 100 ng/mL).
^
10,
31
^

**
*Secondary outcome*
**

*Disability*

The RMDQ (Roland–Morris Questionnaire) is a 24-item patient-reported instrument that is intended to evaluate pain-related impairment resulting from LBP. Every item has a value of 0 if left blank or 1 if approved, therefore producing a total score between 0 and 24, with higher scores denoting greater impairment.
^
32
^ Whereas absolute reliability (Standard Error of Measurement, SEM) is estimated between 1.7 and 2.0 points, test-retest reliability usually falls within an intra-class correlation range of 0.79-0.88.
^
33
^

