## Participant timeline

### Sample size

The sample size for this trial was determined based on methodological standards used in low back pain research. Previous studies have indicated that randomized controlled trials in chronic low back pain require a minimum of 152 participants to detect clinically meaningful superiority differences, with a significance level (α) of 0.05, statistical power of 80%, and a 95% confidence interval. Considering potential attrition, we plan to recruit additional participants to ensure adequate statistical power and robustness of findings.
^
34,
35
^

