### Data analysis

Data will be analyzed based on its nature. Calculation and data auditing will be done using Microsoft Excel 2016. Data will be analyzed by SPSS version 23, and R-4.2.1 for Windows. Eligibility for parametric analysis will be checked using bell’s curve, skewness, kurtosis, Kolmogorov–Smirnov test and Shapiro–Wilk test. Continuous variables will be represented by using an arithmetic mean and standard deviation. Categorical data will be represented by percentage (%) and frequency. Baseline characteristics between groups will be compared using chi-square tests for categorical variables and independent t-tests or Mann–Whitney U tests for continuous variables, depending on data distribution. Normality will be assessed using the Shapiro–Wilk test. For within-group comparisons across time points (baseline, 2 months, and 6 months), repeated measures ANOVA will be applied for parametric data, with Greenhouse–Geisser correction if sphericity is violated; the Friedman test will be used for non-parametric data. Between-group differences over time will be analyzed using mixed-model repeated measures ANOVA, which accounts for group × time interactions, or generalized estimating equations (GEE) if assumptions are not met. Post-hoc pairwise comparisons will be adjusted using Bonferroni correction. Effect sizes (Cohen’s d or partial eta squared) will be reported to indicate the magnitude of differences. All analyses will be conducted at a two-tailed alpha level of 0.05, and intention-to-treat principles will be applied to handle missing data.

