## Discussion

There is an increasing concern of LBP and vitamin D deficiency for chronic pain suffers that is leading the working people towards disability and inefficiency to work.
^
5
^
^,^
^
9
^ A non-randomized quasi experimental study
^
10
^ found therapeutic exercise and vitamin D oral supplementation is effective to reduce pain, replenish vitamin D3 level with short term results. Our study will meet the necessity of randomized systematic evaluation of therapeutic exercises and vitamin D supplement compensation in two different approaches, either by sun exposure, nutrition and healthy lifestyle or by taking oral supplements. We will evaluate outcome in both short term (2 months) and long-term effect after 6 months of stopping the intervention. The experimental group is the therapeutic exercise and booklet group because we assume a positive lifestyle and exercise can replace the role of oral medication supplement, as these were derived as a predictor in observational studies.
^
9
^

The methodological standard of the proposed trial adheres to the Enhancing the QUAlity and Transparency Of health Research (EQUATOR) guidelines to ensure the rigor of the study. As this is a two tailed hypothesis, we assume any treatment can be superior or both may have similar effect. The similar effect is also a positive finding, because oral vitamin D supplement have some adverse effects if taken for longer durations.
^
12
^ Moreover, if the study would have four arms including two interventions, a group with only vitamin D supplement and another with therapeutic exercise and a placebo vitamin D supplement, that could ensure true effects. However, researchers had to limit the study considering funding, scope of practice and complicated management issues. As outcome indicators pain and vitamin D3 levels will be used as primary outcomes and disability as secondary outcome, because previous research suggests disability as a consequence.
^
36
^ BPI measures not only pain severity, but also pain affective interference and pain physical interference,
^
10
^
^,^
^
30
^ that is consistent to the effect of intervention.

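### Two primary outcomes are tested at 0.05 with no success rule, so the stated 5% alpha and 80% power cannot both hold

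*Protocol article*

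**What the plan says.** The Abstract gives two primary outcomes: "Primary outcomes include pain intensity measured by the Brief Pain Inventory (BPI) and serum 25(OH)D3 levels". The Outcome measurement section lists the same two, and the Discussion repeats that "pain and vitamin D3 levels will be used as primary outcomes and disability as secondary outcome".

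The BPI score is described in different ways. The Abstract refers to pain intensity. Outcome measurement describes the whole instrument, "comprising fifteen items, evaluates the degree of pain and how it affects everyday living". The Discussion supports the choice of instrument by noting that "BPI measures not only pain severity, but also pain affective interference and pain physical interference".

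On testing, the Data analysis section states: "All analyses will be conducted at a two-tailed alpha level of 0.05". It compares the groups over time with a mixed-model repeated measures ANOVA containing a group × time term, or with GEE if assumptions fail. Bonferroni is specified for post-hoc pairwise comparisons and nowhere else.

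The Introduction expects the booklet arm to do better on pain, vitamin D and disability, "with these effects observed at both 2 and 6 months following baseline recruitment". No visit is called primary.

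The Sample size section relies on earlier back-pain trials, which are said to "require a minimum of 152 participants to detect clinically meaningful superiority differences". It attaches an alpha of 0.05 and 80% power to that number, but names no outcome, effect size, standard deviation or allocation ratio.

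**The concern.** With two primary outcomes, the error rate and the power of the trial depend on what counts as success. If a significant result on either outcome is enough, two tests at 0.05 give more than a 5% chance of a false claim. If both must be significant, alpha is protected, but the chance of success is below the power of each single test. The protocol does not choose between these rules, yet it fixes 0.05 for every analysis and quotes one power of 80%.

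A split result is plausible, because the arms aim to raise vitamin D by different routes: a capsule in one, sun and diet in the other. If 25(OH)D favours the supplement arm and pain favours the booklet arm, the protocol gives no rule for the overall conclusion. The open choice of BPI score and of visit or contrast leaves further room to decide what is primary after the results are known.

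**Working it through.** **Inputs from the protocol article.** Two primary outcomes (Abstract, Outcome measurement, Discussion); two-sided alpha 0.05 for all analyses (Data analysis); minimum total of 152, alpha 0.05, power 80% (Sample size).

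**Assumptions, not in the document.** 1:1 allocation, so 152 / 2 = 76 analysed per arm; 80% power for each primary outcome at 0.05; a two-group comparison of means; correlation between the two test statistics from 0 to 0.8.

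**Step 1. The plan's own figure.** With no effect size or standard deviation, 152 can be neither reproduced nor refuted. Solving backwards by the normal approximation, the detectable standardised difference is (1.960 + 0.842) × √(2/76) = 0.454 SD. The t distribution gives 0.457 SD. So 152 fits one endpoint, tested once, at about 0.457 SD.

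**Step 2. Either primary suffices.** With no true difference on either outcome and independent statistics, the false-positive rate is 1 − 0.95² = 9.75%. With correlated statistics, the bivariate normal gives the second column below. Power for at least one success is 2 × 0.80 minus the joint power.

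**Step 3. Both primaries required.** The false-positive rate is at most 5%. Joint power is 0.80² = 64% under independence and rises with correlation.

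| Correlation | False-positive rate, either | Power, either | Power, both |
|---|---|---|---|
| 0 | 9.8% | 96% | 64% |
| 0.3 | 9.5% | 93% | 67% |
| 0.5 | 9.1% | 91% | 69% |
| 0.8 | 7.8% | 87% | 73% |

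No row gives both a false-positive rate of 5% and a power of 80% under either rule.

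**Step 4. The visits.** Two outcomes at two visits, all four tests unadjusted, would give about 15% to 17% by simulation (visit correlation 0.5 to 0.7, outcome correlation 0 to 0.3). That is not the plan. With Bonferroni over the two visits within each outcome, the same simulation gives about 8% to 9%, in line with the two-outcome figure in Step 2.

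**Step 5. Repairs at 76 per arm.**
- At 0.025 per outcome, 80% power is reached at about 0.504 SD (t distribution; 0.500 by the normal approximation).
- At 0.457 SD and alpha 0.025, power is about 71%. Restoring 80% would need about 93 per arm.
- Requiring both outcomes with 80% joint power under independence means √0.80 = 89.4% power for each, which needs about 100 per arm.

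The per-arm numbers are patients analysed, before attrition.

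**The case against.** The best defence is that success rules are often left to a statistical analysis plan, which may exist but is not shown. That would excuse silence. Here, however, the protocol itself sets 0.05 for all analyses, confines Bonferroni to post-hoc comparisons and states a power, and these do not fit two primary outcomes.

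The rest of the defence limits how far the point goes, and it stands. Four stronger readings are tempting, and the document does not support them.

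- **Each visit is a separate test at 0.05.** The visits enter one group × time model per outcome, with Bonferroni on the post-hoc comparisons. The 15% to 17% figure therefore does not describe this plan. What remains is that no primary visit or contrast is named.
- **Several BPI scores are each tested.** The text is unclear about which score counts, but it never says that several will be tested. A figure of 1 − 0.95⁴ = 18.5%, for three BPI scores plus vitamin D, would rest on tests that are not stated and on an independence that is implausible for scores from one questionnaire.
- **The Introduction requires every outcome to win at both visits.** It expresses an expectation, and it includes disability, which is secondary. The Discussion also allows either treatment to be superior, or both to be similar. Power for an all-outcomes, all-visits rule is therefore not a property of this plan.
- **Alpha and power both fail whatever the rule.** If either outcome suffices, power exceeds 80%; if both are required, alpha is at most 5%. Only the pair cannot be kept together.

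**Conclusion.** The concern holds in this limited form. With two primary outcomes at 0.05 each and no success rule, the protocol cannot deliver both 5% alpha and 80% power. The false-positive rate is about 8% to 10% if either outcome suffices; power is about 64% to 73% if both are needed. These ranges assume equal power of 80% per outcome and a correlation of 0 to 0.8. The document supports neither assumption with data, and 152 is tied to neither outcome. The undefined BPI score and the unnamed primary visit or contrast add to the problem, but no number can be put on them from the text. This should be settled before unblinding, because the confirmatory claim cannot be interpreted without it.

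**What to change.** Before group identities are revealed to the analysts, amend the protocol to:

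1. State what counts as success across the two primary outcomes, including how a split result will be read.
2. Name one BPI score and one primary visit or contrast.
3. Control alpha across the primaries, either by a fixed sequence with each test at two-sided 0.05, or by testing each at 0.025 (Bonferroni, or Holm starting at 0.025).
4. Restate the Sample size section to match. If 1:1 allocation is confirmed, 152 analysed give 80% power for about 0.457 SD on one endpoint at 0.05, or about 0.504 SD at 0.025.

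The cost is protocol wording, with no extra patients. In a fixed sequence, the second outcome cannot be claimed if the first fails. With the alpha split, power at 0.457 SD falls to about 71%, or a larger difference must be accepted as the target.

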## Introduction

Chronic Low back pain (CLBP) is identified as one of the leading contributors to global disease burden.
^
1
^ It is a commonly prevalent musculoskeletal condition among non-communicable diseases in all countries, ranging from developing to developed countries, and in all age groups from children to the elderly population; affecting almost everyone during their lifespan.
^
2
^ About 55–80% of people suffer from low back pain (LBP) in their lifetime, and the worldwide yearly cost of managing chronic LBP is estimated to be a trillion dollars.
^
3
^ The incidence of LBP is linked to several biopsychosocial aspects, including mechanical, traumatic, pathological and degenerative causes; bone health is known to be associated with both degenerative and mechanical types of LBP.
^
4
^ Approximately 50% of patients seeking treatment for LBP of over 3 months’ duration are found to be additionally suffering from vitamin D and other nutritional deficiencies.
^
5
^ One study suggests a mean decrease of vitamin D levels may increase overall body pain.
^
6
^ A systematic review reported that vitamin D has the potential to decrease pain and inflammation by modifying sensory neuron excitability and anti-inflammatory and pro-inflammatory cytokines. Alongside pain remission, vitamin D levels are linked to increases in muscle strength, which contribute to improving function in patients with LBP.
^
7
^ A strong relationship between LBP and decreased vitamin D levels is noted in elderly women. However, it is still debated whether low vitamin D can predict severe LBP in the general population.
^
8
^ The urban population monograph is moving towards a more sedentary lifestyle and extended sitting hours with almost 12 hours spent in sedentary office jobs in Bangladesh, and this is combined with less exposure to sunshine for city dwellers. This has led to an increased number of LBP cases with insufficient serum vitamin D levels in Bangladesh; those with a sedentary lifestyle and obesity form the majority of sufferers.
^
9
^

A quasi-experimental study shows that therapeutic exercise and vitamin D supplements can be a promising treatment to battle these LBP cases
^
10
^; however the study didn’t elaborate a specific protocol. Other studies suggest that aerobic exercise (low, moderate, high), stretching, balance, motor control exercises, core stability, coordination, muscular strength exercises, and flexibility programs are types of exercises that have a significant outcome on LBP. But because of the intricacy of LBP, it is uncertain which of these types of exercises has the best outcome for rehabilitation; this calls for more in depth studies.
^
10
^
^,^
^
11
^ Research also recommend the necessity of active rehabilitation, including therapeutic exercise (TE), which is emphasized in evidence-based guidelines for the therapy of CLBP, but there is no universal agreement on the most efficient type of exercises.
^
12
^

Vitamin D supplementation can be provided by different approaches including natural approaches, lifestyle education and oral vitamin D supplementation. However, it has been demonstrated that engaging in any type of regular physical exercise increases circulating vitamin D and upregulates the vitamin receptor expression in muscles.
^
13
^ An educational booklet is an effective intervention approach for health-care professionals to deliver regular education concerning the causes, mechanisms, natural history, and prognosis of LBP, and promote the benefits of physical activity and exercise.
^
14
^ In previous studies, booklets on lifestyle, exercise and sun exposure
^
14
^
^,^
^
15
^ or exercise and vitamin D3 supplementation
^
16
^ have found to be effective for CLBP. Therapeutic exercise and vitamin D supplements are effective for the Dhaka city dwellers in Bangladesh,
^
10
^ and creating an educational booklet can be a great solution to raising awareness of CLBP with vitamin D deficiency.
^
9
^ Educational booklets on exercise, sun exposure and healthy nutrition have proven to be promising in other studies.
^
14
^
^,^
^
15
^ From the researcher’s knowledge, no study comparing the use of “vitamin D supplements” or “booklet education on sun exposure, nutrition and lifestyle” along with therapeutic exercise for CLBP cases has been done.

Chronic low back pain (CLBP) has been associated with vitamin D deficiency, which affects calcium metabolism, bone health, and muscle function. Deficiency may lead to osteomalacia, muscle weakness, and impaired neuromuscular control, increasing spinal instability and pain. Additionally, low vitamin D levels can elevate pro-inflammatory cytokines, intensifying pain sensitivity and contributing to chronic musculoskeletal disorders.
^
8
^ Clinical studies have reported a higher prevalence of vitamin D deficiency among patients with CLBP compared to healthy controls, suggesting a potential association between deficiency and pain severity.
^
17,
18
^ Vitamin D supplementation has been explored as a supportive measure in CLBP due to its role in bone health, muscle strength, and inflammation regulation.
^
19
^ Correcting deficiency may improve musculoskeletal function and reduce pain sensitivity, with clinical trials reporting symptomatic improvement in deficient patients.
^
20,
21
^ However, meta-analyses indicate limited overall efficacy, suggesting benefits may be restricted to those with confirmed deficiency, while excessive intake carries risks such as hypercalcemia and kidney stones.
^
22
^

This study hypothesizes that multidimensional comprehensive management through therapeutic exercise combined with an education booklet on sun exposure, nutrition, and lifestyle (TEB) will be superior to therapeutic exercise with oral vitamin D supplementation (TED) in patients with chronic low back pain and vitamin D deficiency. Specifically, it is expected that participants in the TEB group will demonstrate greater improvements in pain symptoms, serum vitamin D levels, and disability status compared to those in the TED group, with these effects observed at both 2 and 6 months following baseline recruitment. Following the study hypothesis, this trial holds clear clinical significance: for clinicians, it offers evidence to guide treatment choices between exercise combined with education or vitamin D3; for patients, it evaluates accessible, low-cost strategies that may improve pain and function; and for researchers, it provides rigorous comparative data to inform future studies on scalable interventions for CLBP.

The specific objectives are:
1.To design a protocol of therapeutic exercise, along with an educational booklet on sun exposure, nutrition and lifestyle, and vitamin D supplementation for the CLBP patients with vitamin D deficiency.2.To evaluate the effectiveness of therapeutic exercise along with an education booklet on sun exposure, nutrition and lifestyle, on painful symptoms, serum vitamin D level and disability for CLBP patients with vitamin D deficiency at 2 months and 6 months post-test compared to baseline.3.To explore the effectiveness of therapeutic exercise along with oral vitamin D supplement on painful symptoms, serum vitamin D level and disability for CLBP patients with vitamin D deficiency at 2 months and 6 months post-test compared to baseline.4.
To study the comparative effectiveness of both groups on painful symptoms, serum vitamin D levels and disability for CLBP patients with vitamin D deficiency at 2 months and 6 months’ post-test compared to baseline.

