The findings of this study may provide important insights into the rehabilitative role of therapeutic exercise in chronic low back pain (CLBP). Beyond its established benefits for musculoskeletal function, exercise may influence the production, absorption, deposition, and overall metabolic function of serum vitamin D, thereby enhancing pain modulation and functional recovery. Evidence suggests that exercise improves vitamin D metabolism and reduces musculoskeletal pain through mechanisms such as modifying sensory neuron excitability and regulating both anti-inflammatory and pro-inflammatory cytokines, ultimately contributing to remission of disability.
^
7
^ If lifestyle education delivered through the booklet demonstrates positive behavioral changes, this could open new avenues for rehabilitation by promoting self-regulation of vitamin D3 levels and supporting natural remission of CLBP. Moreover, the combined approach of therapeutic exercise and supplementation may offer strategies to reduce recurrence or delay the episodic pattern of pain, adding to the repertoire of non-pharmacological options for CLBP therapy. Overall, these findings highlight the potential to broaden rehabilitative strategies by combining exercise-mediated regulation of vitamin D metabolism with conventional physiotherapy, thereby introducing innovative, evidence-based approaches for the management of chronic low back pain.

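### Objectives 2 and 3 judge each arm's effectiveness by change from its own baseline, which a trial of two active arms cannot support

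*Protocol article*

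**What the plan says.** The Introduction of the protocol article lists four objectives. The first concerns designing the intervention protocol; the other three are evaluative. Objective 2 is "To evaluate the effectiveness of therapeutic exercise along with an education booklet on sun exposure, nutrition and lifestyle" and objective 3 is "To explore the effectiveness of therapeutic exercise along with oral vitamin D supplement on painful symptoms". Both are judged on pain, serum vitamin D and disability "at 2 months and 6 months post-test compared to baseline", with no other group as comparator. The comparison of the two arms is a separate objective 4.

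The Data analysis section matches this split. "For within-group comparisons across time points (baseline, 2 months, and 6 months), repeated measures ANOVA will be applied for parametric data", with the Friedman test as the non-parametric alternative. Separately, "Between-group differences over time will be analyzed using mixed-model repeated measures ANOVA", with generalized estimating equations as fallback.

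Under Interventions, both groups receive the therapeutic exercise programme, and the arms differ in the booklet or the supplement. The Discussion says of additional arms: "a group with only vitamin D supplement and another with therapeutic exercise and a placebo vitamin D supplement, that could ensure true effects". It adds that funding, scope of practice and management issues ruled them out. It later says: "The findings of this study may provide important insights into the rehabilitative role of therapeutic exercise in chronic low back pain (CLBP").

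**The concern.** A before-after change in one treated group is not an estimate of a treatment effect. It also contains natural course, placebo response, season and regression to the mean. Season matters for vitamin D: the Randomization section gives December 2022 to May 2023 as the recruitment window, and patients are measured again at 2 and 6 months. Regression to the mean matters because 25(OH)D is both an entry criterion (below 20 ng/mL) and a primary outcome.

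The plan nevertheless uses the word effectiveness for these changes, gives them hypothesis tests at the 5% level and does not label them descriptive. If it is followed as written, the report will contain effectiveness conclusions for each regimen that the design cannot support. One arm may also reach significance and the other not, which is easily misread as a difference between arms. Because exercise is common to both arms, the trial carries no contrast that isolates its effect.

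**Working it through.** **The plan's own figure.** The Sample size section gives a minimum of 152 with two-sided alpha 0.05 and 80% power, but no difference or SD, so 152 cannot be rebuilt from stated inputs. With 1:1 allocation (assumed), 152/2 = 76 per arm, and the implied standardised difference is (1.960 + 0.842) × √(2/76) = 0.454. Only the 76 is used below.

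**Inputs.** From the article: entry cut 20 ng/mL, alpha 0.05 two-sided, n = 76 per arm. Assumed: normal 25(OH)D in the source population with mean μ and SD σ, correlations between repeated measurements, and no treatment effect. A paired t test at one follow-up stands in for the within-group repeated measures test.

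**Formula.** Let S be the screening value, B the baseline and F the follow-up. The expected within-arm change is

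(ρ_SB − ρ_SF) × (μ − E[S | S < 20]), where E[S | S < 20] = μ − σλ, λ = φ(c)/Φ(c) and c = (20 − μ)/σ.

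Which sample serves as baseline decides the answer.

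**Case A: the screening value is the baseline** (ρ_SB = 1, ρ_SF = r). The variance of the change is (1 − r)²σ²(1 − cλ − λ²) + σ²(1 − r²).

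- μ = 20, σ = 8, r = 0.8: λ = 0.798, mean baseline 13.62, rise 0.2 × 6.38 = 1.28 ng/mL. SD of change = √(0.04 × 23.26 + 64 × 0.36) = 4.90. Noncentrality 1.28/(4.90/√76) = 2.27. Probability of p < 0.05: 0.61.
- μ = 25, σ = 10, r = 0.7: λ = 1.141, mean baseline 13.59, rise 0.3 × 11.41 = 3.42 ng/mL. SD of change = √(0.09 × 26.85 + 100 × 0.51) = 7.31. Noncentrality 4.08. Probability 0.98. Simulation that also excludes values below 3 ng/mL gives a rise of 3.2 and 97%.
- μ = 18, σ = 7, r = 0.9, simulated with the same lower limit: rise 0.40 ng/mL, significant in 19% to 21% of arms across runs.

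**Case B: a fresh baseline sample, constant correlation** (ρ_SB = ρ_SF). The expected change is 0, and simulated rejection is about 5%.

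**Case C: a fresh baseline sample, correlation decaying with time.** With ρ_SB = 0.9, baseline to follow-up 0.8 and ρ_SF between 0.75 and 0.80, simulated rejection is 11% to 62% over the population settings tried.

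**Between-arm check.** In 5,000 simulated trials of the first setting in Case A, the within-arm tests rejected in 62% of trials in each arm, and the between-arm test of change in 4.9%. Exactly one arm was significant in 47% of trials, although the arms did not differ.

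**Which case applies?** The Eligibility criteria require documented deficiency. In Recruitment and study procedure, the blinded assessor draws blood after final screening. Table 1 puts eligibility under enrolment and vitamin D under baseline. This order leans towards a separate sample, but no section says whether the qualifying value is also the baseline value.

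**Pain and disability.** The Eligibility criteria set no BPI or RMDQ threshold, so this calculation does not carry over to them.

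**The case against.** The strongest reply is that the trial does not rest on these tests. The hypothesis in the Introduction is between-arm, the Methods aim is comparative, objective 4 has its own group × time analysis, and objective 3 only says that it will explore. The Data analysis section does not itself call the within-group tests evidence of efficacy, and the Discussion openly names the missing arms. All of this stands, and it limits the point to objectives 2 and 3. It does not remove it: these are two of the three evaluative objectives, they are worded as effectiveness, and they have planned tests. Disclosing that arms are missing does not give an uncontrolled comparison a control.

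The size can fairly be challenged too. A reader might infer that both within-arm tests will probably be significant whatever the truth. The documents do not support that: for 25(OH)D it depends on an unstated fact about the baseline sample, and the lower end is the nominal 5%; for pain and disability there is no figure.

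A reader might also infer that the authors plan to claim an effect of exercise. The Discussion text is hedged and specifies no test of exercise, so the fault is a missing caveat, not a planned false claim.

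Finally, replacing tests by confidence intervals does not remove the bias, since a 95% interval that excludes zero is the same paired test. That is correct, so the intervals must be labelled descriptive.

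**Conclusion.** The point holds for objectives 2 and 3. Change from baseline in either arm cannot show that the regimen is effective, whether or not regression to the mean is present, because nothing in the design separates treatment from time.

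For serum 25(OH)D, regression to the mean alone gives a false within-arm finding in about 5% to about 97% of trials with 76 patients. The range reflects the unstated choice of baseline sample and assumed population means, SDs and correlations. It should not be quoted as an expected error rate.

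It would go too far to say that the main comparison fails for this reason: regression to the mean acts on both arms alike, and the between-arm test kept about 5%. It would equally go too far to call that comparison simply protected by randomisation. The Study setting section delivers the experimental arm at one centre and the control arm at another, while the Randomization section stratifies by centre. If each arm has its own centre, centre and arm cannot be separated.

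**What to change.** - Reword objectives 2 and 3 as describing the change from baseline in each arm.
- Report mean change with a 95% confidence interval as descriptive only, with a sentence that it is not evidence of a treatment effect.
- Remove the within-group repeated measures ANOVA and Friedman tests as a basis for effectiveness claims.
- Base all effectiveness conclusions on the between-arm group × time comparison (objective 4).
- State whether the qualifying 25(OH)D value or a later sample is the baseline.
- In the Discussion, state that the trial cannot isolate the effect of exercise because both arms receive it.
- Reconcile the Study setting and Randomization sections on whether both arms are delivered at each centre.

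Apart from the last item, the cost is wording and slightly less analysis; data collection and sample size do not change. The last item is also wording if both arms run at each centre. If they do not, it is a design limitation that has to be reported.
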